## Severity of dyspepsia symptoms

The severity of eight dyspepsia symptoms, including postprandial fullness, early satiation, upper abdominal bloating, epigastric pain, epigastric burning, nausea, vomit, and belching, will be assessed at baseline, once every week in treatment period and at weeks 8, 12, and 16. The severity of each symptom is scored as asymptomatic (0 point), mild (1 point), moderate (2 points), or severe (3 points) [31].

## Quality of life (QoL)

Disease-specific QoL will be assessed at baseline and at weeks 4, 8, and 16 after randomization using 25-item Nepean Dyspepsia Index (NDI) [32, 33], which consists of four domains: interference (13 items); know/control (7 items); eat/drink (3 items); and sleep/disturb (2 items). Each item is measured with a 5-point Likert scale ranging from “not at all” to “extremely.” Higher scores indicate a better QoL.

## Depression and anxiety

Anxiety is linked to PDS [34]. Depression and anxiety symptoms will be assessed at baseline and at weeks 4, 8, and 16 after randomization using the Hospital Anxiety Depression Scale (HADS) [32, 33]. HADS is a self-reported inventory including anxiety and depressive subscales, and each subscale consists of seven questions with scores in the range of 0–21. Higher scores indicate worse symptoms.

## Blinding assessment

To test the patient-blinding effects, all patients will be asked to guess whether they have received acupuncture or sham acupuncture within 5 min after the first treatment session and the sixth treatment session in week 2.

## Credibility and expectancy

Credibility and expectancy of patients will be assessed using the Credibility/Expectancy Questionnaire [35] within 5 min after the first treatment.

The schedule of enrolment, intervention, and assessments is shown in Fig. 3.

**Fig. 3 Fig3:**
[figure not shown]
Schedule of enrollment, intervention, and assessments of this study protocol. AFT after the first treatment, w week

### Adverse events

Any AEs will be monitored and recorded by patients, acupuncturists, and outcome assessors using a preassigned questionnaire throughout the trial. Based on their potential association with the acupuncture needling procedure, AEs will be categorized by acupuncturists and related specialists as treatment-related or not within 24 h of occurrence. Common treatment-related AEs include local bleeding, subcutaneous hematoma, itching at the sites of needle insertion, continuous post-needling pain, dizziness, and so on.

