### Masking

Due to the nature of acupuncture, masking of acupuncturists is quite difficult to achieve. Patients, outcome assessors, and statisticians who perform the statistical analyses will be blinded to group assignment. Participant’s allocated intervention will be not revealed until the statistical analysis is completed.

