### Interventions

Treatment will be performed by licensed acupuncturists who have at least three years of experience in acupuncture. All the acupuncturists will be trained how to locate acupoints and non-acupoints, puncture, and manipulate needles before the trials. Sterile disposable acupuncture needles (length: 25–40 mm, diameter: 0.25 mm; Hwatuo, Suzhou, China) will be used. Both the acupuncture and sham acupuncture treatments will consist of 12 sessions with 20-min duration over four weeks (three sessions per week, ideally every other day). Acupuncture will be discontinued if the patients suffer from any adverse events (AEs). Other treatments which may affect the dyspepsia symptoms will be prohibited, such as antacids, prokinetics, non-steroidal anti-inflammatory drugs, antidepressant drugs, and so forth.

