#### Secondary outcomes

OTE at other time points

Response rate according to OTE and the elimination rate of all three cardinal symptoms will also be measured at weeks 8, 12, and 16 after randomization.

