## Discussion

PDS impacts patients’ QoL and causes a financial burden for society. This large trial will evaluate the efficacy of acupuncture versus sham acupuncture in improving the symptoms of PDS.

This trial meets the methodological demand of adequate randomization and allocation concealment, blinding of patients, outcome assessors, and statisticians. A suitable control group is critical for a well-designed clinical trial. On the basis of literature review, superficial insertion at non-acupoints is the most commonly used approach for administering sham treatments among acupuncture trials [26]. Additionally, the amount of acupuncture is intensive, which is similar to clinical practice in China. Needles will be stimulated manually for at least 30 s at each acupoint and retained in place for 20 min. The treatment frequency is three sessions weekly.

The limitation of our trial is recall bias of pre-treatment symptom severity at the assessment of overall OTE. However, OTE is a reliable and frequently used outcome [27], which has been used as the primary outcomes in several trials [28–30]. Second, the acupuncturists are not blinded for the nature of intervention. Moreover, the use of a fixed block randomization may lead to block size exposure, which may not prevent selection bias from the prediction of treatment allocation in patients. At the end of this trial, we hope the results will provide more reliable evidence and clarify the value of acupuncture as a treatment for PDS.

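### Unmasked acupuncturists help decide which adverse events are treatment-related, so any comparison of treatment-related events by arm is open to attribution bias

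*Protocol article*

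**What the plan says.** The Adverse events section separates recording from attribution.

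- **Recording** is shared: "Any AEs will be monitored and recorded by patients, acupuncturists, and outcome assessors using a preassigned questionnaire throughout the trial".
- **Attribution** is narrower. "Based on their potential association with the acupuncture needling procedure", it says, "AEs will be categorized by acupuncturists and related specialists as treatment-related or not within 24 h of occurrence".

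The same section gives local bleeding, haematoma, itching where the needle went in, continuing pain after needling and dizziness as common treatment-related events.

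On masking, the Masking section says: "Due to the nature of acupuncture, masking of acupuncturists is quite difficult to achieve". The Discussion repeats it as a limitation: "the acupuncturists are not blinded for the nature of intervention". The masked groups are named: "Patients, outcome assessors, and statisticians who perform the statistical analyses will be blinded to group assignment". The related specialists are not among them.

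On treatment: "Treatment will be performed by licensed acupuncturists who have at least three years of experience in acupuncture". Under Acupuncture, needles are manipulated to reach De qi. Under Sham acupuncture, they penetrate 2–3 mm at non-acupoints without that manipulation. Both arms therefore receive real skin penetration.

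**The concern.** Whether an event was caused by treatment is a judgement. Here it is made partly by people who know whether the patient had manipulated needling or shallow sham needling. Because both arms are needled, bruising, pain or dizziness can follow a session in either. Someone who believes that sham needling is inert may call dizziness unrelated after sham and related after acupuncture. Someone with a stake in the safety of acupuncture may do the opposite. The article gives no reason to expect one direction rather than the other.

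At stake is the meaning of a table of treatment-related events by arm. If the label is applied differently in the two arms, the table can show a difference where the event rates are equal, or hide one where they differ. Relatedness is the only classification of adverse events that the article describes, so such a table is a likely form of reporting.

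**Working it through.** The document gives no figure to reproduce. The check sets its statements side by side and then gives an illustration under assumed rates.

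**1. Who takes part, and are they masked?**

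| Role | Records events | Classifies relatedness | Masking stated |
|---|---|---|---|
| Patients | yes | no role stated | masked |
| Outcome assessors | yes | no role stated | masked |
| Acupuncturists | yes | yes | not masked |
| Related specialists | no role stated | yes | not stated |

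The two groups stated to be masked help to capture events but have no stated part in attribution. Of the two groups that attribute, one is unmasked and the other is not described. The specialists cannot be counted as a masked safeguard, nor can it be said that they are unmasked.

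**2. Where is there room for judgement?** The criterion is association with needling. On the natural reading that sham needling counts, a bruise or itch at a needle site is related in either arm and leaves little discretion. Of the five common events listed, four are tied to needle insertion and one, dizziness, is not. The exposure lies mainly with events of that second kind.

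**3. How large could the effect be?** From the article: n = 140 per arm (Sample size), and Fisher's exact test at two-sided 0.05 as one of the tests for categorical variables (Statistical analysis). Assumed, because the article gives neither: the proportion r of patients with an event, equal in both arms, and the proportions a and b of those events labelled related in each arm.

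The observed related rates are r × a and r × b. The probability of a significant result is the sum, over all counts i and j from 0 to 140, of Bin(i; 140, ra) × Bin(j; 140, rb) where Fisher's p for (i, j) is below 0.05.

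Each cell shows the related rates in the two arms, then the probability of a significant difference:

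| r | a = b = 80% | a = 80%, b = 60% | a = 90%, b = 50% |
|---|---|---|---|
| 5% | 4.0 v 4.0; 2.1% | 4.0 v 3.0; 3.2% | 4.5 v 2.5; 7.5% |
| 10% | 8.0 v 8.0; 2.9% | 8.0 v 6.0; 6.2% | 9.0 v 5.0; 18.4% |
| 20% | 16.0 v 16.0; 3.4% | 16.0 v 12.0; 12.3% | 18.0 v 10.0; 42.5% |

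With equal labelling, the test stays below its nominal 5%. With unequal labelling, the error rate rises with the event rate and with the gap in labelling. It matters little when events are rare or the gap is small. The last column needs a very large gap, and point 2 suggests that most needle-site events would not show one. The comparison of all events uses r in both arms and does not depend on a or b.

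**The case against.** The strongest reply is that the document contains no error or contradiction here. Acupuncturists do not classify alone, and every event is recorded whatever its label, partly by masked patients and outcome assessors. A data and safety monitoring board reviews progress every three months, and the lack of acupuncturist masking is a declared limitation. All of this stands, and it limits the point to the relatedness label. It does not remove the point, because none of these safeguards is stated to mask the attribution.

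Three stronger readings are tempting and are not supported.

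- **That each acupuncturist judges the events of their own patients.** This is plausible, but the article says only that acupuncturists treat and that acupuncturists take part in classification. It does not link the two for a given patient.
- **That the trial's safety conclusion rests on a test of related events between arms.** The article states no such test and does not list adverse events among its primary or secondary outcomes. The analysis of adverse events may sit in an analysis plan that is not shown, so its absence is no fault.
- **That the 24-hour limit worsens the bias**, because visits are spaced and follow-up outcomes "will also be measured at weeks 8, 12, and 16 after randomization". The limit is the same in both arms, so it does not by itself create a difference in attribution. Patients also record events between visits, and needling events cluster around sessions. At most this is a question of compliance.

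It can also be objected that a judge of relatedness often needs to know where the needle went, and the two arms use different points. That is a genuine limit on how well the judgement can be masked.

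**Conclusion.** The point holds in a limited form. The article assigns the relatedness decision to unmasked acupuncturists together with specialists whose masking is not stated, while both arms are needled. Any comparison of treatment-related events by arm is therefore open to attribution bias, mainly for events away from the needle site.

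The size is unknown. Under the assumed rates above, with moderately unequal labelling (80% v 60%), the chance of a false significant difference is 3.2% to 12.3%, against 2.1% to 3.4% with equal labelling. These figures show what unequal labelling could do and are not an estimate of what will happen. The direction cannot be predicted. The primary and secondary efficacy outcomes are not affected, and a comparison of all adverse events is not affected by the label. This is a modest safety-assessment point that is worth acting on because the remedy is cheap.

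**What to change.** 1. Have the related specialists already named make the relatedness decision, and state that they are masked to arm. They should work from a short event description that omits the allocation, needle depth and manipulation. The acupuncturist supplies facts only and does not vote on the label.
2. Make all adverse events by arm, regardless of attribution, the main safety comparison, with treatment-related events as supportive.

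The cost is a change of wording in the protocol and the adverse event form, plus one short written description per event. The needle site may sometimes still reveal the arm, so masking of the specialists will be imperfect. The article says that recruitment is under way, so the first change can apply to events still to come. The second needs no new data, because all events are already to be recorded.

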### Data management

All researchers including acupuncturists, outcome assessors, and statisticians will receive training regarding data management. Data will be inputted into the electronic case report form (eCRF) which will be established before recruitment. The clinical research associates are responsible for verifying the accuracy of data. Online monitoring will be used in this trial. With the support of the “check” function in the eCRF, dynamic management will be implemented to ensure that the data are collected completely, promptly, and accurately. Data lockup will be implemented by the data management team on completion of the study. The researchers will then be unable to modify the data.

All research documents, including both the paper files and electronic documents, will be preserved for at least five years after publication. If reviewers or readers have any questions regarding our published data, they can contact the corresponding author for access to the original data. The private information of patients—including name, telephone number, and ID number—will be anonymous to ensure participant confidentiality.

In addition, an independent Data and Safety Monitoring Board (DSMB) will be established to review and interpret data generated from the study. The DSMB will review the progress of the trial every three months independently from investigators and the sponsor and decide on any premature closure of the study. The members of Data and Safety Monitoring Board are listed in Additional file 3.

### Quality control

The trial protocol is reviewed and revised by the experts in acupuncture, gastroenterology, methodology, and statistics. Prespecified standard operating procedure—including intervention, details in filling eCRF, assessment of outcomes, data management—will be used to train the related staff. An inspection plan will be designed for quality control. Health education and timely follow-up will also be made to improve the compliance of patients. For participants who discontinue acupuncture or deviate from protocol, the outcome assessors will still try to assess the outcomes.

### Statistical methods

#### Sample size

Since acupuncture is a complex intervention, it is different from drugs. The efficacy of acupuncture will be altered, if the acupoints in the study are changed. For this reason, literature data speculation is not adopted in this trial. Based on previous clinical experience, the proportions of acupuncture and sham acupuncture responders for OTE are expected to be 55% and 35%, respectively. For elimination of all the three symptoms, the proportions are expected to be 26% and 10%, respectively. A two-sided significance level is 0.05. A sample size of 224 (112 patients in each group) was estimated to have at least 80% power to detect significant differences. The power was calculated as the product of the power of each endpoint: 82.5% and 84.3%. To compensate for a 20% attrition rate, the sample size expands to 140 patients in each group.

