### Randomization and allocation concealment

All eligible patients will be randomly assigned to the acupuncture group or sham acupuncture group in a 1:1 ratio with a central web-based randomization (Beijing Guide Technology Co., Ltd.). The blocked randomization sequence will be computer-generated with the SAS 9.3 software by a professional statistician, who is not involved in the implementation and statistical analysis of the trial. The clinical research coordinator will be responsible for enrolling patients, obtaining informed consent and requesting randomization.

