### Outcomes

#### Primary outcomes

The two primary outcomes are the response rate based on overall treatment effect (OTE) and the elimination rate of all three cardinal symptoms: postprandial fullness; upper abdominal bloating; and early satiation (no symptoms) at the end of treatment (four weeks after randomization) [26].

When assessing OTE, outcome assessors will evaluate patients using a 7-point Likert scale. The question is “How were your gastric symptoms during the past week in comparison with the baseline period?”, which closely resembles the way physicians evaluate treatment benefit in clinical practice. The answers will include “extremely improved,” “improved,” “slightly improved,” “not changed,” “slightly aggravated,” “aggravated,” and “extremely aggravated” [26]. Patients who answer “extremely improved” or “improved” will be considered as responders. Although there is no universally accepted primary outcome established for therapeutic trials in FD, OTE is a frequently used outcome [27], which has been used as the primary outcome in several trials [28–30].

The elimination rate of three cardinal symptoms was added as another primary outcome. Because the U.S. Food and Drug Administration has argued against the use of OTE as a single primary outcome for its recall bias. After trial commencement, the Data and Safety Monitoring Board (DSMB) suggested that we could use combined primary outcomes for our study. Similarly, the pattern of two primary outcomes was adopted in a study evaluating acotiamide in FD [26]. The elimination rate is based on the severity of dyspepsia symptoms [31] and is defined as the proportion of patients whose scores of postprandial fullness, upper abdominal bloating, and early satiation all decline to 0 [26].

Acupuncture will be considered as an effective therapy, only if both primary outcomes achieve significant difference to avoid type I error accumulation. All protocol amendments are described in detail in Additional file 2.

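### The claimed power of at least 80% contradicts the plan's own figures: 82.5% × 84.3% = 69.5% for the rule that both primary outcomes must be significant

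*Protocol article*

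**What the plan says.** The Sample size section of the protocol article sets the assumptions. For the overall treatment effect (OTE), "the proportions of acupuncture and sham acupuncture responders for OTE are expected to be 55% and 35%, respectively". For the second outcome, "For elimination of all the three symptoms, the proportions are expected to be 26% and 10%, respectively". The test level is fixed too: "A two-sided significance level is 0.05".

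From these it concludes: "A sample size of 224 (112 patients in each group) was estimated to have at least 80% power to detect significant differences". It then states the method: "The power was calculated as the product of the power of each endpoint: 82.5% and 84.3"%. The total is raised to 140 per group to allow for 20% attrition.

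The success rule is in the Primary outcomes section: "Acupuncture will be considered as an effective therapy, only if both primary outcomes achieve significant difference to avoid type I error accumulation".

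**The concern.** When both outcomes must be significant, type I error is protected without splitting alpha. The price is paid in power, because the trial fails if either test fails. Joint power is therefore lower than either separate power, and the sample size has to be set on the joint figure. The plan recognises this, since it says the power is a product, yet the value it reports is not that product. A figure of at least 80% fits each endpoint separately but not the rule that decides the trial.

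At stake is the planned type II error. Readers are told it is at most 20%; on the plan's own figures and method it is about 30%. If one endpoint narrowly misses, the result could be given more weight as negative evidence than the design supports. According to the Primary outcomes section, the elimination outcome was added after the trial had started, and the Trial status section says recruitment is continuing. The true power of the two-outcome rule should be on record before results are known. Neither the treatment effect estimate nor the type I error is affected.

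**Working it through.** **Inputs** (all from the protocol article)

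- Two-sided alpha 0.05, n = 112 per group (Sample size); 1:1 allocation (Randomization and allocation concealment)
- OTE response 55% v 35%; elimination 26% v 10% (Sample size)
- Attrition 20% (Sample size)
- Success requires both outcomes (Primary outcomes)

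**Step 1. Reproduce the two endpoint powers.** The continuity-corrected normal approximation is

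power = Φ[(|p₁ − p₂| − 1/n − 1.96·SE₀) / SE₁], with SE₀ = √(2p̄(1 − p̄)/n) and SE₁ = √((p₁(1 − p₁) + p₂(1 − p₂))/n).

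- OTE: p̄ = 0.45, SE₀ = 0.0665, SE₁ = 0.0651. (0.2000 − 0.0089 − 0.1303)/0.0651 = 0.933, so power = 82.5%.
- Elimination: p̄ = 0.18, SE₀ = 0.0513, SE₁ = 0.0502. (0.1600 − 0.0089 − 0.1006)/0.0502 = 1.005, so power = 84.2%.

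The first matches the stated 82.5% and the second is within 0.1 point of the stated 84.3%. The attrition step also reproduces: 112/0.80 = 140.

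**Step 2. Take the product the plan describes.** 0.825 × 0.843 = 0.6955. The chance of missing at least one endpoint is 1 − 0.6955 = 0.3045.

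**Step 3. Does another test explain the 80%?** At 112 per group, two-sided 0.05:

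| Test | OTE | Elimination | Product |
|---|---|---|---|
| Continuity-corrected | 82.5% | 84.2% | 69.5% |
| Fisher's exact (named in Statistical analysis) | 82.8% | 85.6% | 70.9% |
| Pooled, uncorrected | 85.8% | 88.2% | 75.6% |
| Uncorrected chi-square, exact power | 86.1% | 89.2% | 76.7% |
| Unpooled | 86.7% | 89.0% | 77.1% |

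None reaches 80%.

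**Step 4. Does correlation between the endpoints explain it?** Treating the two test statistics as bivariate normal with the stated powers, joint power is:

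| Correlation | 0 | 0.3 | 0.5 | 0.9 | 0.95 |
|---|---|---|---|---|---|
| Joint power | 69.5% | 71.7% | 73.5% | 78.9% | 80.2% |

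Reaching 80% needs a correlation of about 0.944. The assumed rates do not permit that. The within-group correlation of two binary outcomes with rates p > q is greatest when every patient with the rarer outcome also has the commoner one, and is then √(q(1 − p)/(p(1 − q))):

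- Acupuncture: √(0.26 × 0.45/(0.55 × 0.74)) = 0.54
- Sham: √(0.10 × 0.65/(0.35 × 0.90)) = 0.45

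The corresponding correlation of the test statistics is (0.26 × 0.45 + 0.10 × 0.65)/√(0.475 × 0.2824) = 0.182/0.366 = 0.50. Here 0.475 and 0.2824 are the sums of p(1 − p) over the two groups for each endpoint. Joint power at that ceiling is about 73–74%.

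**Step 5. What would give 80%?** With the continuity-corrected formula and independent endpoints:

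- n = 132: 0.886 × 0.902 = 79.9%
- n = 133: 0.889 × 0.904 = 80.4%; 133/0.80 = 166.25, so 167 randomised per group
- n = 140, no data lost: 0.905 × 0.919 = 83.2%

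Fisher's exact test needs 130 evaluable (163 randomised) per group; the uncorrected pooled test needs 122 (153).

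**The case against.** The arithmetic cannot be disputed, but four points can be made for the plan.

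- **The 30% sits at the pessimistic end.** Both outcomes rate the same patients' gastric symptoms at week 4, so positive correlation is likely. This stands: the shortfall should be given as about 26–30%. It does not restore 80%.
- **More than 112 per group may contribute.** The analysis includes everyone randomised, uses multiple imputation, and tries to follow patients who stop treatment. This stands in part. If attrition is below 20%, joint power lies between 69.5% and 83.2% under independence. But the plan attaches its claim to 224 patients and adds the rest only to offset losses, and imputation recovers at most part of the information lost with missing outcomes.
- **A less conservative test narrows the gap.** An uncorrected test at the maximum correlation gives 78.6% by the normal approximation and about 79.5% by simulation. That is close to 80%, but it takes the most favourable choice on both counts. It is also not the calculation the plan reports. Fisher's exact test is a valid choice and is not the error.
- **The 80% may have been meant per endpoint.** The sentence alone could be read that way. The next one says the power was a product, so the text does not support that reading.

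It is also fair to say that nothing in the article shows a null result would be misread. That consequence is a risk, not a certainty.

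**Conclusion.** The concern holds. The claim of at least 80% power is wrong for the trial's only success rule, and the contradiction lies between two adjacent sentences of the Sample size section, with no outside figure needed. With 112 evaluable patients per group and the assumed rates, joint power is 69.5% under independence, which is what the plan's product implies. It is about 74% at the largest correlation those rates allow. The type II error is thus about 26–30%, not at most 20%. Joint power passes 80% only if clearly more than 112 per group are evaluable: about 133 with the plan's formula under independence, with 83.2% at a full 140. The separate endpoint powers and the inflation to 140 are correct.

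**What to change.** Correct the power statement in the Sample size section before results are known. It should say that, at 112 evaluable per group, power is 82.5% for OTE response and 84.3% for symptom elimination taken separately. It should add that the power to win on both is about 70% assuming independence, rising to about 83% if all 140 per group provide complete data. The phrase about at least 80% should be removed or tied expressly to each endpoint alone. This costs one sentence and a less favourable headline figure; it makes the text true but leaves the planned joint power at about 70%.

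If the sponsor wants 80% for the two-outcome rule, the sample size must be recalculated. The plan's own formula gives about 133 evaluable and 167 randomised per group at 20% attrition. That is 334 in total against 280, or 54 more patients, and would need a protocol amendment while recruitment continues. Accepting the lower power or enlarging the trial is the sponsor's choice; the choice should be stated. No change of test is needed to correct the error.
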